#### Behavioral economic measures

The modified Activity Level Questionnaire measures past-month activity frequency and enjoyment with Likert scales and separate items for substance-related and substance-free activities [34]. The frequency and enjoyment ratings are multiplied to obtain a cross-product score that reflects reinforcement derived from the activity. The variables of interest will be the average reinforcement from all substance-free activities (substance-free total) and the total reinforcement ratio, i.e., substance-related total/(substance-free total + substance-related total). Reinforcement ratio values have been shown to mediate response to brief alcohol interventions with emerging adults [24]. We modified this measure to also measure time allocation to each activity and perceived constraints on access to the activity. We also ask several open-ended questions about participants’ goals regarding hobbies, service, and community activity participation. This information will be used to provide activity suggestions as part of the SFAS intervention.

The Alcohol Purchase Task (APT) [43] is a simulation measure that assesses self-reported alcohol consumption and financial expenditure across a range of drink prices (alcohol demand). Participants report the number of standard drinks they would consume in a hypothetical drinking scenario across 17 price increments ranging from zero (free) to $20 per drink. Demand curves are estimated by fitting each participant’s reported consumption across the range of prices to Hursh and Silberburg’s [44] demand curve equation: ln *Q* = ln *Q*0 + *k* (*e*-*αQ*0*C* − 1), where *Q* is demand, *Q*0 is the level of demand that occurs when cost, *C*, approaches zero, *K* specifies the range of *Q*, and *α* is a measure of demand curve elasticity. Several demand metrics are generated from the demand curve which reflect individual differences in strength of alcohol as a reinforcer [43], and the proposed analysis will focus on the three indices that have shown the most robust associations with alcohol-related outcomes [34]: (1) intensity of demand (alcohol consumption at the lowest price), (2) Omax (maximum financial expenditure on alcohol), (3) elasticity of demand (sensitivity of alcohol consumption to increases in cost) [34, 43]. Demand curve indices from The Alcohol Purchase Task (APT) will be used as secondary outcomes and mediators of treatment.

Delay discounting (DD) will be measured with a computerized monetary choice questionnaire (ED 50) in which participants repeatedly choose between a larger fixed amount of hypothetical money ($1000) available after a delay and variable smaller amounts of hypothetical money that are available immediately [45].

#### Aversive emotional states and coping

The Depression, Anxiety, and Stress Scales (DASS) [46] will be used to provide feedback to participants in the SFAS condition and to determine whether these symptoms moderate outcomes and change following treatment. The Brief COPE [47] will be used to assess coping at baseline to generate feedback on effective coping resources that will be included in the SFAS. Changes in coping will also be assessed as a secondary outcome variable.

#### Drinking and drinking norms

The NIAAA Drinking Assessment will be used to assess past-year alcohol consumption including drinking frequency, typical number of drinks, maximum number of drinks, and frequency of binge drinking. For each item, participants are given a range of frequencies (e.g., every day to 3–11 times in the past year) or a range of drinks (e.g., 1 drink to 25 or more drinks) to choose from. This measure will be administered at baseline and again at 12 months.

Perceived normative drinking will be assessed with the Drinking Norms Rating Form, and the Protective Behavioral Strategies Survey (PBSS) [48] will be used to measure the use of 15 protective behavioral strategies commonly used to reduce alcohol-related harm. Protective behavioral strategies will also be evaluated as a mediator of treatment outcomes.

#### Personal values

The two-part, 22-item Valued Living Questionnaire [49] assesses both the degree to which a participant values each of eleven domains of life importance (e.g., family relations, spirituality, physical well-being) on a 10-point scale (1 = not at all important, 10 = extremely important) and the degree to which the participant’s past-week actions are consistent with these values on a 10-point scale (1 = not at all consistent, 10 = extremely consistent). Personalized feedback on values and consistent actions is included in the SFAS session.

#### Attention check questions

By providing only one logically correct answer per question (e.g., “To answer this question, please choose option number four”), the five question Conscientious Responders Scale assesses whether participants are attentively answering questions, rather than answering them haphazardly or randomly [50]. We included this scale so study staff would have a clear measure of respondent conscientiousness (4/5 CRS questions answered correctly) and a marker of data quality.

## Study oversight

Oversight of internal monitoring of the participants’ safety will be conducted by the PI, [name]. [name] has significant experience conducting clinical research of brief alcohol interventions. The Data and Safety Monitoring Plan for this application will begin by implementing standard procedures for day-to-day monitoring of the study by the Investigators and study staff. Investigators [name] and [name] and project director [name] will also meet weekly to evaluate the progress of the trial, to review data quality, recruitment, and study retention, and to examine other factors that may affect outcomes. They will also review participant experiences and the rates of adverse events (AEs) to determine any necessary changes to reduce participant risk. [name] will be responsible for distinguishing serious from nonserious adverse events and providing attributions (causality and severity). [name] will report any serious adverse events (SAEs) in writing within 48 h to the NIAAA Project Officer as defined by NIAAA and to the University of Memphis IRB following their policies. [name] will apprise fellow investigators and study personnel of all adverse events that occur during the conduct of this research project through regular study meetings. An annual report will be submitted to the NIAAA project officer summarizing all adverse events. A brief report will be generated quarterly for the study record. If necessary, the investigators will make appropriate recommendations for changes in protocol.

## Interim analyses

In order to preserve power and reduce the likelihood of type 1 error, we will not conduct formal *inferential* interim or futility analysis [51]. Given the nature of interventions we are studying (brief behavioral approaches that have been used previously with no adverse effects) and our target sample (young adults who are not seeking treatment or at risk for alcohol withdrawal), we think that it is extremely unlikely that we would need to stop the trial due to clear evidence of harm or overwhelming evidence of benefit. Adopting an inferential approach to interim analysis would thus unnecessarily undermine our ability to detect our planned moderate effect size outcomes at study conclusion without increasing risk of type one error (if we do not adjust alpha based on interim analyses) or type two error (if we do adjust alpha to accommodate interim analyses).

However, co-investigator and study biostatistician [name] will conduct descriptive interim analyses after we have enrolled 75 participants in each condition. The study will be stopped if one of the following three scenarios manifests: (1) there is clear evidence of harm; (2) there is no likelihood of demonstrating treatment benefit (futility); (3) there is overwhelming evidence of the benefit of treatment. Although we do not expect any physical risks with this research, if psychological risks are occurring at a frequency that is higher than expected (more than 5% of participants are experiencing moderate to severe distress or troublesome feelings associated with the questionnaires or interventions), enrollment and interventions will be promptly halted until a safety review is completed by the study investigative team in conjunction with the University of Memphis IRB and the NIAAA Program Officer.

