## Sample size and power

We have focused our power analysis using Monte Carlo simulations [64] with population estimates and patterns of missingness from our previous trial [24]. These models from our previous trial used generalized mixed models which covaried gender and race/ethnicity, taking into account clustering by individual and therapist. Based on the Monte Carlo estimates comparing BAI + SFAS to control (within *d* = 0.83/0.71, between *d* = 0.33/0.32), we are proposing to recruit 525 subjects (175 per group) for the study. Assuming a similar pattern of attrition as our previous trial will result in *n* = 362 (69%) complete cases, *n* = 95 (18%) cases missing one data point; *n* = 37 (7%) cases missing two data points; *n* = 21 (4%) cases missing three data points; and *n* = 11 (2%) cases missing four data points. We calculated power via Monte Carlo simulations by determining the proportion of 1000 replications for which the null hypothesis that a parameter was equal to zero was rejected for each parameter at alpha = 0.05 (i.e., probability of rejecting the null hypothesis when it is false). This resulted in the following power estimates for typical drinks/problems: treatment effect of BAI + SFAS vs. control = 1.00/1.00; mediation via proportionate substance-free reinforcement = 0.90/0.99; mediation via negative affect = 0.85/0.93; mediation via alcohol demand: 1.00/1.00. While our proposed sample size would not be sufficient to detect very small effects, we believe such small effects are likely to have little clinical meaning in terms of the variables we are assessing in the present trial, and the necessary sample size to detect such effects would be very large (> 1000).

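### The plan declines inferential and futility interim analysis, then makes stopping for futility or overwhelming benefit mandatory after a descriptive look with no boundary

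*Protocol article*

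**What the plan says.** All of this stands in the Interim analyses section of the protocol article, except the last item.

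- First paragraph: "In order to preserve power and reduce the likelihood of type 1 error, we will not conduct formal *inferential* interim or futility analysis". The reason given is that "Adopting an inferential approach to interim analysis would thus unnecessarily undermine our ability to detect our planned moderate effect size outcomes". The authors add that an unadjusted look raises type I error and an adjusted one raises type II error. They consider a stop for harm or for overwhelming benefit very improbable.
- Second paragraph: the study biostatistician "will conduct descriptive interim analyses after we have enrolled 75 participants in each condition". Then: "The study will be stopped if one of the following three scenarios manifests: (1) there is clear evidence of harm". The other two scenarios are that "there is no likelihood of demonstrating treatment benefit (futility); (3) there is overwhelming evidence of the benefit of treatment".
- The only number attached to any halt is a safety trigger: "more than 5% of participants are experiencing moderate to severe distress or troublesome feelings associated with the questionnaires or interventions". It leads to a pause for review and is not an efficacy or futility rule.
- Sample size and power: the null hypothesis "was rejected for each parameter at alpha = 0.05", with 175 per group and no allowance for an interim look.

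**The concern.** The two paragraphs cannot both be followed. Finding futility or overwhelming benefit means judging outcome data by treatment and acting on the result. Calling the look descriptive does not change that, because the stopping sentence is unconditional.

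Two different things are at stake. A stop for benefit gives the trial a second chance to declare success, and the plan allots no alpha to it. A stop for futility gives the trial a second chance to fail, which costs power. These are the two harms that the first paragraph says the plan avoids. The trigger also counts people enrolled rather than people followed up, so the data at the look would be thinner than 75 per condition suggests.

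**Working it through.** **Is there a figure to reproduce?** The plan gives no interim boundary or alpha split. Its stated power for BAI + SFAS against control is 1.00/1.00 at d = 0.33/0.32. A simple two-sample formula, Z = d / sqrt(2/175), gives Z = 3.09 and 2.99, hence power 0.870 and 0.849. A baseline-adjusted mean of four follow-ups gives 0.998 to 1.00 if correlations of 0.3 to 0.7 are assumed. The stated figure is therefore attainable, and the simple-formula powers below are illustrative.

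**Type I error from the benefit stop.** Inputs: 75 of 175 per arm, so t = 75/175 = 0.43 if information follows enrolment (assumption). The final test is unadjusted at 0.05, taken as two-sided (the sidedness is not stated), for one comparison. The interim and final statistics are bivariate normal with correlation sqrt(t), and overall alpha = 1 − P(|Z1| < c, |Z2| < 1.96). Since follow-up will be incomplete, smaller t is shown too.

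| Threshold in effect at the look | t = 0.43 | t = 0.20 | t = 0.15 |
|---|---|---|---|
| p<0.05 | 0.085 | 0.092 | 0.094 |
| p<0.01 | 0.055 | 0.058 | 0.058 |
| p<0.005 | 0.052 | 0.054 | 0.054 |
| p<0.001 | 0.0503 | 0.0507 | 0.0507 |

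**Effect of the futility stop.** At t = 0.43, stopping when the interim Z is below 0, 0.5 or 1.0 (illustrative cuts) changes one-sided type I error from 0.025 to 0.024, 0.023 or 0.019. Simple power at d = 0.33 falls from 0.870 to 0.864, 0.843 or 0.784.

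**Data available at the look.** Trial status gives a recruitment start of 8 December 2021 and completion expected by the end of June 2025, which is 42.7 months. Even accrual is assumed.

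- Rate: 525/42.7 = 12.3 per month, or 4.1 per arm.
- The 225th participant enters at month 225/12.3 = 18.3.
- Number per arm past month k: (18.3 − k) × 4.1, before dropout.
- Power at a single visit: P(Z > 1.96 − 0.33/sqrt(2/n)).

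| Visit | n per arm | Power at d = 0.33 | 95% CI half-width for d |
|---|---|---|---|
| Month 1 | 71 | 0.50 | 0.33 |
| Month 3 | 63 | 0.46 | 0.35 |
| Month 6 | 50 | 0.38 | 0.39 |
| Month 12 | 26 | 0.22 | 0.54 |

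**A controlled version for comparison.** O'Brien-Fleming-type spending at t = 0.43 spends 2 × (1 − Φ(1.96/sqrt(0.43))) = 0.0028 at the look. This gives an interim boundary of |Z| > 2.99 and a final test at p<0.0489, for overall alpha 0.050. At t = 0.30 the boundary is |Z| > 3.58, with a final test at p<0.0498.

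**The case against.** The case for leaving the section alone has four parts.

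- **The word formal leaves room for informal monitoring, and nothing says outright that arms will be compared.** This softens the conflict. It does not remove it, because futility and benefit cannot be found without looking at outcomes by treatment, and the stop is mandatory.
- **Thresholds, outcomes and contrasts belong in the full protocol or analysis plan, which are not shown.** This stands: their absence from an article is not in itself an error. The contradiction remains, since a boundary set elsewhere would conflict with the first paragraph, and no boundary would leave the second paragraph uncontrolled.
- **Overwhelming is a strong word, and the authors think such a stop very improbable.** This also stands. A reader might infer that the trial runs at 8.5% type I error, or that its 0.05 cannot be defended. The document does not support that: 8.5% needs overwhelming to mean p<0.05, and a reading near p<0.001 leaves alpha at about 0.050.
- **Futility need not rest on 12-month data.** A reader might take the 26 per arm, with power of 0.22, to show that futility could not be judged at all. The Intervention outcome analyses section fits one model to all four follow-ups, and the earlier visits are fuller. A reader might also suppose that the futility stop inflates type I error; it lowers it slightly.

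**Conclusion.** The contradiction is on the page and holds. The section rejects inferential and futility interim analysis and then requires a stop on either ground, while the power calculation keeps the full 0.05.

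The numerical consequence is bounded but not known. For one two-sided comparison, the benefit stop takes overall alpha to somewhere between about 0.050 and 0.094, depending on a threshold the article does not state and on the information available at the look. The lower end is negligible. Applying the stop to several outcomes or contrasts would add to this. The futility stop leaves type I error intact and costs power, from less than one percentage point to about nine for the cuts tried.

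Follow-up would be incomplete at the look, so a futility judgement would rest on limited data, though on more than the 12-month completers alone. These figures assume even accrual, no dropout, a two-sided test and the simple two-sample formula.

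**What to change.** **Preferred.** Delete the futility and overwhelming-benefit scenarios so that the look is descriptive only, as the first paragraph intends. Leave the harm provision unchanged. Alpha then stays at 0.05 with no adjustment and no change in sample size. The cost is a wording amendment and the loss of an undefined option to stop early, which for benefit the plan itself regards as very improbable.

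**If a benefit stop is kept.** Revise the first paragraph so that it no longer denies an inferential look. Name one outcome and one contrast, and attach an alpha-controlling boundary, for example O'Brien-Fleming-type spending at information 0.43: interim |Z| > 2.99, final p<0.0489. Recompute the boundary from the information actually available. Make any futility rule non-binding and trigger it by completed follow-up rather than enrolment. The cost is a slightly smaller final alpha and a later futility look.

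**Either way.** Under even accrual, month 18.3 falls in about June 2023, before the article was published in March 2024, so the look may already have taken place. If so, record its date, what was seen by arm and what was decided, and report this with the results.

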## Statistical analyses

Statistical analyses will be performed using Mplus version 8.4 and SPSS version 26. The distributions of continuous variables including drinking outcomes, mediators, and potential covariates will be examined. Due to the nature of the multi-wave data collection, some participant attrition is inevitable. We will carefully examine the extent and pattern of missing data and will evaluate attrition effects by testing whether systematic differences exist between those who complete all study measures versus those who do not. In instances when a small amount of data is missing from a measure (i.e., < 10%) and relevant missing data correlates are included, data will be assumed to be missing at random, and a robust maximum likelihood estimator will be used (MLR) [52]. The MLR estimator adjusts standard errors and chi-squares/loglikelihoods to accommodate missing data, non-normal distributions, and nesting by individuals and clinicians. Missing not at random models will also be estimated to determine whether the models are robust to the missing at random assumption of maximum likelihood estimation [52, 53]. In the evaluation of intervention outcomes, we will use intention-to-treat analysis. In our prior studies using similar intervention procedures 99% of participants completed all intervention sessions [28, 54].

### Preliminary analyses

Preliminary data analyses will include studies of patterns of missing data, dropout rates, therapist adherence, distributional properties of measures, and correlations among outcome measures. Outliers greater than 3.29 standard deviations (SDs) above or below the mean will be recoded to one unit above or below the highest or lowest nonoutlier value [55]. Second, we will use latent growth curve modeling (LGCM) to model trajectory shapes and assess growth rates over time and individual differences in the growth rates as a function of intervention. While the first approach will allow us to examine if and when the effects start to decay, the LGCM approach will inform us of the overall pattern of changes across time and allow us to test if the trajectory shapes differ between the control and the intervention conditions. With five measurement time points, we will be able to estimate trajectory shapes accurately beyond a straight linear trajectory. Linear and non-linear trajectory will be investigated to accurately model the trajectory shape supporting the hypotheses on intervention effects, as the outcomes may not decrease constantly as a function of time. As such, we will investigate the declining or plateauing measurement time points and model non-linear trajectory (e.g., piecewise, quadratic growth).

### Intervention outcome analyses

Consistent with our previous approaches [24], evaluation of our intervention outcomes will occur via generalized linear mixed models with a negative binomial distribution and log link function (due to our expectation that the primary drinking outcomes will be skewed and zero-inflated). These models will (A) evaluate change in the primary drinking outcomes (drinks per week , past-month binge drinking, and alcohol-related problems) and (B) evaluate change in secondary outcomes (increases in proportionate reinforcement from substance-free activities and self-regulation, reductions in alcohol demand, drug use, and negative affect) across the four follow-up time points (1-, 3-, 6-, and 12-month) as a function of time and treatment condition. Time will be centered at the 1-month follow-up (time = 0 at 1-month follow-up) and baseline levels of the outcome will be included as a covariate. Random slope effects (i.e., time-by-treatment interactions) will be explored; however, our previous trial found they were not significant and were eliminated from the final reported models. Thus, we anticipate that final models will be estimated using a compound symmetry covariance matrix with random intercepts and linear effects of time. Age, gender, and ethnicity will be included as covariates due to their association with drinking level and the possibility of differential treatment response [56]. Models will be run with the following planned contrasts: active treatment versus education control, BAI + SFAS versus education control, RT + SFAS versus education control, and BAI + SFAS versus RT + SFAS. To test the hypothesis that no differences in outcomes will be found between the two active treatments, the two one-sided test (TOST) procedure for testing equivalence/noninferiority will be used [57]. Based on this approach, equivalence is established at the α significance level if a (1–2α) × 100% confidence interval for the difference in efficacies (RT + SFAS—BAI + SFAS) is contained within the equivalence margin or the interval (-δ, δ). This equivalence margin, *δ*, reflects the range of values for which treatments are “close enough” to be considered equivalent [57]. We have chosen the value *δ* = 1.12, for alcohol use, and *δ* = 0.82 problems, based on 75% the lower limit of a confidence interval of the difference between the BAI + SFAS against the assessment only in our previous trial [57–59].

